### Recruitment {15}

Working through the public health system, keeping in mind the proximity of the ASHAs to the community, it is expected that adequate participant enrolment can be achieved. Monitoring and supervision by the project team will assist in timely completion. The time period of recruitment is from February to May, 2024. After the recruitment, the randomization will be done and intervention will be administered for 6 months. Expected to finish by November 2024 and endline assessment in December 2024.

## Assignment of interventions: allocation

### Sequence generation {16a}

Allocation of intervention and sequence generation will be as follows. Codes will be randomly assigned to the four interventions (ASHA, m-health, ASHA + m-health, and control groups) namely A, B, C, and D. In the next step, randomization list will be generated using RANDOM ALLOC software. Eighteen subcenters will be randomized into 4 study groups (A, B, C, and D) using different permutations of ABCD. Each subcenter will be allocated random numbers ranging from 1 to 18 using random number generators and random shuffling of this number. Interventions will be allocation to the subcenters in the sequence of random shuffled numbers as per the randomization list.

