**Methods:**

The intervention is a 2 × 2 factorial design trial applying two interventions individually and in combination with 1:1 allocation ratio: (i) ASHA-led medication adherence initiative comprising of home visits and (ii) m-health intervention using reminders and self-reporting of medication use. This design will lead to four potential experimental conditions: (i) ASHA-led intervention, (ii) m-health intervention, (iii) ASHA and m-health intervention combination, (iv) standard of care. The cluster randomized trial has been chosen as it randomizes communities instead of individuals, avoiding contamination between participants. Subcenters are a natural subset of the health system, and they will be considered as the cluster/unit. The factorial cluster randomized controlled trial (cRCT) will also incorporate a nested health economic evaluation to assess the cost-effectiveness and return on investment (ROI) of the interventions on medication adherence among patients with CVDs. The sample size has been calculated to be 393 individuals per arm with 4–5 subcenters in each arm. A process evaluation to understand the effect of the intervention in terms of acceptability, adoption (uptake), appropriateness, costs, feasibility, fidelity, penetration (integration of a practice within a specific setting), and sustainability will be done.

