## Methods: participants, interventions, and outcomes

### Study setting {9}

The study will be implemented in the ENDIRA (Epidemiology of Non-communicable Diseases in Rural Areas) cohort (n-114,064 individuals) which includes 2064 patients with heart disease in whom adherence to drugs for heart disease has already been assessed. The ENDIRA cohort is spread over 5 primary health centers consisting of 18 subcenters where the health details of all individuals have been recorded. In order to avoid contamination in the treatment allocation and its response, at least 10 km of distance among villages will be maintained and they will be clubbed into 4 groups.

The intervention will be implemented in Angamaly block consisting of five local self-government areas namely Mookkannoor, Kalady, Thuravoor, Karukutty, and Manjapra with a population of 18,638, 20,407, 20,475, 26,811, and 14,668 in Ernakulam district [20] in Kerala state, India, respectively.

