### Concealment mechanism {16b}

It will be an open-label trial as concealment is not possible. However, study site allocation will be done only after completing baseline assessment and agreements with sites to participate.

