## Statistical methods

### Statistical methods for primary and secondary outcomes {20a}

Several models will be run to test for the main outcomes, implementation outcomes, and related research questions. Mixed linear and logistic effects models as appropriate will be used to identify differences between the groups (ASHA, ASHA and m-health, m-health, control group), where random effects will be used for the clusters and fixed effects will be used for effects of ASHA workers and of m-health. The primary dependent variable in the models will be change in adherence measured by the Morisky scale. Models will also be fitted for the secondary outcomes such as change in blood pressure, random blood sugar, Hba1c levels, and quality of life. Subsequently, covariates such as age, sex, and co-morbidities will be added to the models to adjust for potential confounders.

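### The allocation balances only the number of subcenters per arm; constraining it on baseline adherence and adjusting for baseline MMAS would improve balance and precision at little cost

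*Protocol article*

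**What the plan says.** Sequence generation {16a} sets out the whole procedure. "Eighteen subcenters will be randomized into 4 study groups (A, B, C, and D) using different permutations of ABCD"; then "Each subcenter will be allocated random numbers ranging from 1 to 18 using random number generators and random shuffling of this number"; and finally "Interventions will be allocation to the subcenters in the sequence of random shuffled numbers as per the randomization list". No stratification, matching or covariate constraint is named. The abstract gives the resulting arm size: "The sample size has been calculated to be 393 individuals per arm with 4–5 subcenters in each arm".

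On timing, Concealment mechanism {16b} states that "study site allocation will be done only after completing baseline assessment and agreements with sites to participate", and Recruitment {15} also puts randomization after recruitment. Study setting {9} describes the cohort as "spread over 5 primary health centers consisting of 18 subcenters" and reports that adherence had already been measured in its 2064 heart disease patients. The same section says that villages will be kept at least 10 km apart and combined into four groups. Sequence generation does not take this up.

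In Statistical methods {20a} the primary dependent variable is change in the Morisky score. The mixed model has random cluster effects and fixed effects for ASHA and m-health. In a later step, "covariates such as age, sex, and co-morbidities will be added to the models".

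**The concern.** All 18 clusters are allocated at one time, after each subcenter's mean MMAS, number enrolled and PHC are known. These are the conditions under which covariate-constrained randomization can be used, yet the stated procedure uses none of this information. With 4 or 5 clusters per arm, chance gaps between arms in baseline adherence can be an appreciable fraction of the 0.4-unit target.

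A change score does not fully remove such a gap. If the slope of endline on baseline is below 1, an arm that starts higher tends to show a smaller change. Baseline MMAS is not among the covariates given as examples, so the article does not say that this will be corrected. An arm may also draw several of its subcenters from one PHC, which ties the arm partly to one local health team. At stake are precision and the credibility of the comparison in a trial whose outcome assessors are not blinded.

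**Working it through.** **Inputs from the article.** 18 subcenters in 4 arms (4.5 on average); target difference 0.4 and SD 1.8; 238 per group before and 393 after the design effect and 10% attrition; 1572 in total, so 1572/18 = 87.3 per subcenter. The ICC, the design effect and the number of subcenters per PHC are not given.

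**Implied ICC.** 238 × 1.5 × 1.1 = 392.7, which rounds up to the stated 393, so a design effect of about 1.5 is inferred. ICC = (1.5 − 1)/(87.3 − 1) = 0.0058. ICCs of 0.02 and 0.05 are assumptions that show the range. (The 238 was not reproduced: 0.4 with SD 1.8 and 80% power gives 318 at two-sided 5%. That is a separate matter and does not affect this check.)

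**Spread of baseline gaps.** Variance of a subcenter mean = 1.8² × [ICC + (1 − ICC)/87.3]. SD of the difference between two arms = √(2 × variance/4.5).
- ICC 0.0058: variance 0.0557, SD 0.157
- ICC 0.02: variance 0.101, SD 0.212
- ICC 0.05: variance 0.197, SD 0.296

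**Allocation as planned.** Permuted ABCD lists were simulated against shuffled subcenters, with at least 40,000 allocations. Arm counts were always 4, 4, 5 and 5.

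| Event | ICC 0.0058 | ICC 0.02 | ICC 0.05 |
|---|---|---|---|
| Some active arm more than 0.2 from control | 44% | 67–69% | 84% |
| Some active arm more than 0.4 from control | 3% | 15% | 39% |
| One given pair of arms more than 0.2 apart | 20–21% | 35% | 50% |
| Two arms against two (main effect) more than 0.2 apart | 7% | 18% | 34% |

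Ranges show differences between runs.

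**From gap to bias.** With a baseline-to-endline slope b, a baseline gap g shifts the unadjusted change estimate by (b − 1) × g. With b = 0.5 (assumed) and g = 0.2, the shift is −0.1, a quarter of the target.

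**PHC.** Under assumed splits of 4/4/4/3/3, 5/4/3/3/3 and 6/4/3/3/2 subcenters, some arm takes three or more subcenters from one PHC in about 36–37%, 42% and 58% of allocations.

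**Constrained allocation, drawn from the best-balanced 10% of 1000 candidates.** Chance that some active arm is more than 0.2 from control:

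| Scoring | ICC 0.0058 | ICC 0.02 | ICC 0.05 |
|---|---|---|---|
| Mean MMAS only | 0% | 1% | 14–17% |
| Equal weight on MMAS, size and PHC | 8–13% | 26–37% | 54–62% |

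The ranges in the second row reflect how the three parts are scaled and the cluster sizes assumed. MMAS-only scoring leaves PHC clustering at about 36–37% (4/4/4/3/3 split). Equal weighting lowers it to about 12–15%.

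**The case against.** Random allocation of clusters is valid as written, and a mixed model with random cluster effects carries chance imbalance in its standard errors. Nothing in the section is misstated. That stands, and it makes this an optional gain.

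Several stronger readings are tempting, and the document does not support them:
- *That the allocation is unrestricted.* Permutations of ABCD fix the arm counts. It is unconstrained only on covariates.
- *That a baseline gap passes one-for-one into the result.* The outcome is change, so only the regression-to-the-mean part carries over. At the implied ICC about two thirds of the variance of a subcenter mean is individual sampling noise (0.0114 of 0.0172), which adjustment for individual baseline MMAS handles well.
- *That baseline MMAS has been left out of the model.* The covariates are introduced as examples, and the final list may sit in an analysis plan that is not shown.
- *That a large imbalance is likely whatever the ICC.* The 44% is the worst of three comparisons at half the target. For one pair it is about 20%, and for the factorial main-effect contrast about 7%. The higher figures rest on ICCs that the article does not give.
- *That PHC imbalance has a known effect on adherence.* No figure in the article allows this to be calculated.

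Nor can shortage of degrees of freedom be held against model adjustment alone. Eighteen clusters in four arms leave about 14, and four PHC indicators would leave about 10. That cost also arises if PHC is used in a constrained allocation and then carried into the model.

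What remains is that the data are available at allocation, the stated procedure does not use them, and using them costs little.

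**Conclusion.** The point holds as a cheap improvement in balance and precision. At the implied ICC of about 0.006, a gap of more than 0.2 between control and some active arm is close to an even chance (44%), while a gap of 0.4 is unlikely (3%). With a slope of 0.5, a 0.2 gap would move an unadjusted change estimate by about 0.1. The result rests on a design effect back-solved from 393, on SD 1.8 applying to baseline MMAS, on near-equal subcenter sizes, and on the assumed slope. PHC clustering is common under every split tried, but an arm of four subcenters cannot cover five PHCs, so it can be reduced and not removed.

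**What to change.** 1. Name individual baseline MMAS as a covariate in the primary mixed model. It is measured on every participant and costs at most about one cluster-level degree of freedom. This step applies even if the allocation has already been drawn.
2. If it has not, replace the shuffle in Sequence generation {16a} with covariate-constrained randomization. Generate a large set of candidate allocations and score each mainly on subcenter mean baseline MMAS, with number enrolled and PHC as further criteria. Keep about the best-balanced 10%, check that no pair of subcenters is always or never together, and draw one at random. State the weights, because the gain in MMAS balance depends strongly on them.
3. Before listing candidates, reconcile the four groups of villages in Study setting {9} with the allocation of 18 single subcenters in {16a}. If those groups are geographic, arm and PHC would be confounded further.

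The cost is some programming by the statistician who already generates the list, with no added data or participants. The downside is that the balancing variables should be reflected in the model, at a cost in cluster-level degrees of freedom, so cluster-level terms should be kept few.

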### Concealment mechanism {16b}

It will be an open-label trial as concealment is not possible. However, study site allocation will be done only after completing baseline assessment and agreements with sites to participate.

### Implementation {16c}

The allocation sequence will be generated by the Statistician, enrolment will be by the Field coordinator and the Field coordinator will assign subcenter as it is a cluster randomized trial.

## Assignment of interventions: blinding

### Who will be blinded {17a}

Data analysts will be blinded. The ASHA workers, patients, and outcome assessors are not blinded.

### Procedure for unblinding if needed {17b}

In this study, the ASHA workers, patients, and outcome assessors will not be blinded. Only the data analysts will be blinded. The data analyst will be unblinded if there are any outlier biochemical values which requires immediate action so that the patient can be intimated.

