**Interventions**									
Intervention A			♦	♦	♦	♦	♦	♦	
Intervention B			♦	♦	♦	♦	♦	♦	
Intervention C			♦	♦	♦	♦	♦	♦	
Intervention D			x	x	x	x	x	x	

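### The data analyst, the only blinded party, is to be unblinded when an outlier biochemical value needs immediate action, although informing the patient takes identity and not arm

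*Protocol article*

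**What the plan says.** Under Who will be blinded {17a} the article states "Data analysts will be blinded" and "The ASHA workers, patients, and outcome assessors are not blinded". Procedure for unblinding if needed {17b} repeats that "Only the data analysts will be blinded" and then gives its one exception: "The data analyst will be unblinded if there are any outlier biochemical values which requires immediate action", for the purpose of telling the patient. It states neither what counts as such a value nor how often one is expected.

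Five other places bear on the rule:

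- Plans for assessment and collection of outcomes {18a}: the ASHA measures glucose with a glucometer, and a laboratory technician reads HbA1c on a point-of-care device.
- Confidentiality {27}: the data are anonymised, with a unique id for each patient.
- Concealment mechanism {16b}: sites are allocated only after the baseline assessment.
- Sequence generation {16a}: "Codes will be randomly assigned to the four interventions (ASHA, m-health, ASHA + m-health, and control groups) namely A, B, C, and D". The 18 subcenters are then randomised to these four coded groups.
- Participant timeline {13}, Table 1: the rows for Interventions A, B and C carry a diamond in months 1 to 6. The row "Intervention D" carries an x in each month, with no key in the text available.

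**The concern.** The rule ties a legitimate aim, telling a patient about a worrying result, to a step that does not serve it. Nothing in the aim requires anyone to learn the study arm. The analyst is also an odd person to route it through, because the people who take the reading have it first.

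The trial is open to patients, ASHAs and outcome assessors, and its primary outcome is self-reported. Masking the analyst is the only blinding left. It protects decisions made once the data are in hand, such as how missing values are treated and how the models are fitted. A protocol article may leave such decisions for later, and that is no fault. But they are the decisions that can drift if the person making them knows which group is which.

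The letters A to D add a smaller difficulty. If the letters in Table 1 are the randomised codes, the table points to D as the arm without intervention. If they are not, the same letters carry two meanings in one document.

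**Working it through.** The article gives no figure on this point, so there is none to reproduce. The check has four steps.

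**1. What informing the patient requires.**

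| Need | Where the article supplies it | Arm needed? |
|---|---|---|
| The value | Read by the ASHA or the technician at point of care ({18a}) | No |
| The patient's identity | Unique id for each patient ({27}) | No |
| Someone to make contact | ASHAs, who are not blinded ({17a}); the field coordinator, who assigns the subcenters ({16c}) | No |

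No step needs the analyst to hold the allocation.

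**2. How often the rule might be triggered.**

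Inputs:
- Planned participants: 4 × 393 = 1,572 (Sample size, under Baseline study).
- Attrition: 10% (same place), so 1,572 × 0.9 ≈ 1,415 at endline.
- Post-allocation biochemical assessments: one. Table 1 puts secondary outcomes at close-out, and allocation follows baseline, so a value found at baseline cannot reveal an arm at that time.
- Rate r of values needing immediate action, per participant: **not in the document; assumed to lie between 0.01% and 1%**.

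Treating participants as independent, and supposing that each such value sets off the rule, P(at least one) = 1 − (1 − r)^n.

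| Assumed r | n = 1,415 | n = 1,572 |
|---|---|---|
| 0.01% | 13% | 15% |
| 0.05% | 51% | 54% |
| 0.1% | 76% | 79% |
| 0.2% | 94% | 96% |
| 0.5% | 99.9% | >99.9% |
| 1% | >99.9% | >99.9% |

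For a 95% chance with n = 1,415, r must be 1 − 0.05^(1/1415) ≈ 0.21%, or about 2 per 1,000.

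The number tested may be smaller. HbA1c is limited to cardiac patients with type 2 diabetes, and the consent section {26b} can be read as limiting blood sugar to them too, although {18a} reads more broadly. The number with diabetes is not given. With an illustrative n of 300, the range is 3% (r = 0.01%) to 95% (r = 1%).

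**3. What one event would reveal.** All participants in a subcenter share an arm, so one patient's arm gives that of the whole subcenter. If the analysis file carries codes A to D, it also gives the meaning of that code for its 4 to 5 subcenters. By itself it does not decode the other three codes.

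**4. Table 1 beside {16a}.** Section {16a} assigns the letters to interventions at random. Table 1 shows one letter, D, marked differently from the rest, which reads naturally as standard of care. The article does not say whether the table's letters are the random codes or labels in listing order; {16a} itself also lists control last. The two places need reconciling whichever is true.

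**The case against.** Five points can fairly be made for the plan.

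- **The word may mean re-identification.** The data are anonymised and the stated purpose is to reach the patient, so unblinding the analyst may mean only linking an id to a person. This is possible. But the sentence stands under the unblinding heading, directly after the statement that only analysts are blinded, so a reader will take it as disclosure of the arm. The same edit settles either meaning.
- **The rule may seldom be used.** If field staff see the value first, they can act before it reaches the analyst. This stands as a limit on step 2, whose probabilities assume that every such value triggers the rule. It also shows that the rule is not needed.
- **The trigger is limited.** A reader might infer that any biochemical outlier unblinds the analyst. The text confines it to values needing immediate action.
- **The main bias lies elsewhere.** With open assessors and a self-reported outcome, most of the risk arises at measurement, and masking the analyst does not remove it. This stands and keeps the point in proportion.
- **Table 1 proves nothing about the code.** A reader might infer that the control code is already public. The x has no key in the text available, and nothing says that the table uses the randomised letters. The documents support a request to reconcile, no more.

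**Conclusion.** The point holds as a badly fixed unblinding rule. As written, it puts the only blinding in the trial at avoidable risk and does nothing for the patient that the field team cannot do by unique id. This conclusion rests on the text and needs no assumed rate.

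The size of the risk is not known. At about 1,415 participants the chance of at least one trigger is about 13% at a rate of 0.01% and over 99.9% at 1%, on the assumptions of independence, one post-allocation assessment and use of the rule for every such value. A reader might infer that blinding is almost certain to be lost. That needs a rate of about 2 per 1,000 or more, which the document does not give. Nor would one event unmask the whole trial: it would reveal one subcenter's arm and at most one code.

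The change is worth making because it costs almost nothing, but the rule is not a threat to the trial as a whole.

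**What to change.** 1. In {17b}, replace the sentence by one to this effect: when a biochemical value needs immediate action, the field team or field coordinator identifies the participant by unique id and informs them, and the data analyst is not given the allocation for this purpose. If re-identification was all that was meant, this wording says so.
2. Give the analyst a file with masked labels for the four arms and for the two factors (ASHA, m-health), different from the letters in Table 1, and open them only once the primary analysis is locked.
3. State beside Table 1 or in {16a} whether the table's A to D are generic labels or the randomised codes, and give the meaning of the x.

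The cost is one sentence, one recoding of labels and one clarifying line. Sample size, visits and burden on participants do not change. No clinical threshold or action is proposed here.

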## Data collection and management

### Plans for assessment and collection of outcomes {18a}

The primary outcome adherence will be measured by Morisky 8-item adherence questionnaire which has been validated in various countries including India and in various disease conditions. The eight-item Morisky Medication Adherence Scale (MMAS-8) is a structured self-report measure of medication-taking behavior that has been widely used in various cultures [25–27].It has a maximum score of 8.

The quality of life will be measured by the EuroQol five‐dimensions – 3‐level (EQ5D) which is a versatile quality of life (QOL) instrument with five dimensions (mobility, self‐care, usual activities, pain/discomfort, and anxiety/depression) and a visual analog scale. The questionnaire has also been found to be valid and reliable in various disease conditions including cardiovascular and cancer in India and neighboring countries [28, 29].Random blood sugar among the patient and family member will be measured by the ASHA as per standard methods using a glucometer. Blood pressure will also be measured using the electronic Blood pressure will be recorded with the OMRON HEM 7124 automatic blood pressure monitor (Shimogyo-ku, Kyoto, Japan) by measuring upper arm BP. A laboratory technician will measure Glycosylated Haemoglobin using the Lumira Dx point of care device.

Real-time data entry will be monitored, and wherever there are difficulties with using the app, support will be provided by the field coordinator.

